### 2.8. Ethical Considerations

The present study has been approved by each of the local research officer’s institutional ethics committees and is registered with ISRCTN clinical trial registry (ISRCTN14582090).

#### 2.8.1. Duty of Care

Given the potential stigma and risk associated with mental health issues, particular care will be taken when members of the project teams engage with employees and employers with mental health issues after informed consent has been received. Although the target groups in the project are comprised of individuals who may be vulnerable, previous European Alliance Against Depression projects have found the interventions being offered to have beneficial effects on mental health without any adverse effects. Therefore, the benefits of participating are expected to outweigh any potential risks. The PHQ-ADS, administered at baseline and follow up, includes an item which addresses suicidal ideation. Participants will be presented with a message at the end of the survey encouraging them to contact their general practitioner (GP), local mental health services or quality-assured support service, or the local research officer if they reported that they have experienced suicidal ideation. Participants in the study will be provided with contact details for the local research officers should they require support. Local research officers and other personnel involved in direct contact with employees and employers in the pilot study will receive special training in relation to general mental health difficulties, and more specifically, depression, anxiety, and suicidal behaviour. They will be provided with supervision in their work setting by the lead investigators in each of the intervention countries on an on-going basis.

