For the purpose of the pilot study, the MENTUPP Hub will be available in the following languages: Albanian, Dutch, English, German, Hungarian, and Spanish. Materials in the MENTUPP Hub will be delivered to participants via three intervention components that participants will navigate through themselves. Intervention component A focuses on promoting mental wellbeing and targeting non- and pre-clinical mental health aspects including stress, burnout, and depressive symptoms. It involves the presentation of materials that develop the participants’ general understanding and awareness of mental wellbeing, stress, and burnout, as well as a mental wellbeing and stress management toolkit. Leader-specific materials relate to organisational factors associated with wellbeing and teaches communication skills to supervisors on how to address psychosocial aspects of work with employees and develop action plans for modifying the psychosocial work environment. Employee-specific materials relate to stress management and peer support in the workplace with practical guidance on how to build peer support structures supported by video case studies of lived experiences.

Intervention component B is focused on depressive disorders and co-morbid anxiety. It is comprised of psychoeducational materials aimed at gaining a general understanding of what depression and anxiety are, as well as what factors are involved in their onset and maintenance. There are useful tips for users and advice on where to seek further help if necessary. A distinct toolkit for supervisors covers more specific topics including the business impact of these mental illnesses, information on suicide prevention, and guidelines for helping employees in different situations.

Intervention component C aims to target stigma in the workplace and is comprised of psychoeducational materials for all users including lay helpers and sufferers. An overview of the aims, content, and delivery of each component are detailed in Table 1.

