In addition, the pre-implementation assessment will capture the enterprise’s activities in relation to mental health as well as company characteristics such as the number of employees, first language spoken by employees, etc. Once an SME has been recruited, the lead investigator and local research officer will deliver a brief introductory session either face-to-face or online (depending on local COVID-19 restrictions) to employees and employers two weeks prior to intervention implementation. The local research officer will describe the purpose of the study, the scope and nature of the intervention tools, an overview of the questionnaire, and will highlight the opportunity for participants to take part in focus groups after completing the intervention. Employees will be explicitly told that their decision to participate will not impact their position within the company in any way and their details will not be shared back with management of the organisation. All potential participants within an SME will be given an information leaflet with basic information about the study and will be given the opportunity to ask any questions. The information leaflet will provide contact details for the local research officer should they have any questions. Following receipt of this information leaflet, participants will be asked to give consent for participation in the study by completing an online form.

**Table 1 ijerph-19-00947-t001:** Overview of the aims, content, and delivery of MENTUPP components.

Module	Aims/Objectives	Material Type(s)	General Material	Sector Specific Versions of the Material	For Employees	For Supervisors
Understanding Mental Wellbeing, Stress and Burnout	To better understand mental wellbeing, stress, and burnout; How to apply 3 approaches for promoting mental wellbeing and preventing mental health problems: proactive, responsive, and reactive; To identify what everyone in the organisation can do to support mental health and wellbeing.	Online written material		YES	YES	YES
Toolkit: Mental Wellbeing and Stress Management	Increase your understanding of mental wellbeing and how it can be strengthened; Increase understanding of stress, how it impacts thoughts and emotions; Introduce practical exercises for managing stress, breathing and mindfulness.	Online written material, reflective exercises, practical exercises		NO	YES	YES

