Three surveys including internationally validated measures tailored to the specific evaluation needs of the MENTUPP pilot study will be used to collect information at the individual level at baseline and follow-up. The pre-intervention survey will be administered to all employees and gather information relating to the following themes: sociodemographic and work-related information; ways of approaching mental health difficulties in the organisation; experience with mental health difficulties; expectations of the MENTUPP intervention; acceptability, appropriateness, and feasibility of MENTUPP at baseline and follow-up; and the impact of COVID-19 on mental health and the workplace. A post-intervention survey for employees will ask participants for specific feedback on their views and experiences of participating in MENTUPP and on their views of the MENTUPP Hub on completion of the intervention period. A post-intervention survey for leaders will assess the extent to which activities recommended by MENTUPP are initiated in the SME (e.g., better work planning, more peer support, regular meetings, etc.).

Log data on user activity tracked via the MENTUPP Hub will be collected to compile information on how frequently the MENTUPP Hub was used and which parts of the platform were most frequently accessed.

Internationally validated questionnaires (listed below) will be administered during facilitated sessions at baseline before access to the MENTUPP Hub is given, and again at the end of the 6-month pilot intervention period. The following self-report, standardised measures of wellbeing and mental health will be included:○Mental wellbeing and quality of life: The World Health Organisation—Five Wellbeing Index (WHO-5) [85]○Depression and anxiety: Patient Health Questionnaire Anxiety and Depression Scale (PHQ-ADS) [86]○Depression stigma: Depression Stigma Scale (DSS) [87]○Presenteeism in the workplace: Stanford Presenteeism Scale (SPS-6) [88]○Productivity: Work Productivity and Activity Impairment—General Health V2.0 (WPAI-GH 2.0) [89]○Burnout: Oldenburg Burnout Inventory (OLBI) [38,90] ○Help-seeking behaviour: Attitudes Towards Seeking Professional Psychological Help-Short Form (ATSPPH) [91]○Presence (level) of psychosocial risk factors and stressors: Selected items and scales from the Copenhagen Psychosocial Questionnaire (COPSOQ) [92]

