### 2.6. Data Management

The survey data will be collected via Qualtrics (Provo, UT), which is a General Data Protection Regulation (GDPR) compliant online platform. Participants will create their own unique identifier that will allow researchers to link their evaluation data to their activity on the MENTUPP Hub. Any personal information collected (e.g., email address/phone number) required in accessing the Hub will be stored separately from evaluation data. The information that participants provide will be aggregated for analysis by SME/sector depending on the number of cases and an individual’s data will not be fed back to SME management. Qualitative data will be collected by local research officers.

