### 2.7. Data Analysis

#### Process and Preliminary Outcome Evaluation

The self-reported surveys (including validated questionnaires) and monitoring instruments collected pre- and post-intervention will be analysed using descriptive statistics and non-parametric and parametric tests. Patterns of completeness in the survey will inform the development of the self-reported surveys (including validated questionnaires) to be used in the cRCT. The log data from the MENTUPP Hub will also be analysed to establish patterns of engagement by calculating the number of participants visiting the Hub more than once, the total number of visits to the Hub overall and on an individual level, and the total time spent accessing and engaging with the content.

Qualitative data of the focus groups will be audio recorded, transcribed, and analysed using thematic analysis [94] to explore patterns in qualitative data across participants and across sectors. Themes and subthemes will be determined as the overarching categories of common data across multiple participants.

Quantitative and qualitative data will be interpreted in relation to each sector as well as each intervention country to understand the implementation of the intervention within each context. This information will be used to optimise the intervention for the cRCT.

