## 3. Discussion

The MENTUPP intervention employs a multilevel approach that focusses on educating supervisors and employees about mental health at work, gives tools to supervisors that can be used to promote mental wellbeing at work and reduce risk factors in the psychosocial work environment, as well as individual oriented tools for coping with stress and supporting peers. Although multilevel approaches are often recommended, high quality studies testing multilevel approaches at the workplace are largely missing [36,70,95,96,97].

The MENTUPP intervention has been developed based on theoretical frameworks [22,23] by leading researchers in occupational mental health from across the EU and Australia. The intervention has involved the co-operation and consultation of key stakeholders in occupational health in the three occupational sectors to ensure that the tools are relevant and specific to their needs. The approach also involves SME management from the very beginning of the implementation of the MENTUPP intervention to encourage support for and uptake of organisational level approaches to improve mental health of employees in SMEs.

The results of this pilot study will provide a comprehensive overview of the implementation of such an intervention in a variety of contexts, languages, and cultures. The overall MENTUPP project will not only provide evidence-informed, tailored tools for employees and managers/owners of SMEs but will evaluate how useful the tools are and better understand the barriers for using these tools in real-life settings across the healthcare, construction, and ICT sectors. Furthermore, given that construction is a male-dominated industry and healthcare is generally female-dominated, this provides us with an added opportunity to understand the implementation of such an intervention with consideration of potential gender differences.

Adverse effects of participating in the pilot study include the effect of potential mental health related stigma and the risks associated with mental health issues [98]. Participants might be hesitant to participate in the pilot study as participation might be perceived to harm their employment. This risk will be mitigated by SME engagement with the online delivery of the MENTUPP Hub that can also be accessed in participants’ own time, and the strict confidentiality with which participant data will be treated with.

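### The support message for suicidal ideation is placed at the end of the survey, so a participant who endorses the item and stops early would not see it

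*Protocol article*

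**What the plan says.** Section 2.8.1 (Duty of Care) of the protocol article notes that the PHQ-ADS, used at baseline and follow-up, has an item on suicidal ideation. It then sets out the response: "Participants will be presented with a message at the end of the survey encouraging them to contact their general practitioner (GP". The sentence goes on to list local mental health services, a quality-assured support service and the local research officer, for people who have reported ideation.

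Support that does not depend on the answer is also described:

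- Section 2.8.1: "Participants in the study will be provided with contact details for the local research officers should they require support". Staff in direct contact with participants are trained in depression, anxiety and suicidal behaviour, and are supervised.
- Section 2.4 (Procedure): "The information leaflet will provide contact details for the local research officer should they have any questions".
- Section 2.5 (Process Evaluation): the validated questionnaires "will be administered during facilitated sessions at baseline before access to the MENTUPP Hub is given", and are given again after the six-month intervention period.
- Section 2.3, on Hub component B: "There are useful tips for users and advice on where to seek further help if necessary".

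On how the survey is run and completed, section 2.6 says: "The survey data will be collected via Qualtrics (Provo, UT"), and section 2.7 says: "Patterns of completeness in the survey will inform the development of the self-reported surveys".

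**The concern.** The message is the only action the article links to an endorsed ideation item. No active follow-up by staff is described, and section 2.8.2 keeps names apart from evaluation data, so the described response relies on the participant seeking help. With the message at the end, receiving it depends on reaching the last page.

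The setting gives some reason to care about early stopping. The Introduction reports elevated suicide risk in construction and health, and describes a culture of self-reliance in male-dominated workplaces that may discourage help-seeking. Section 3 (Discussion) adds: "Participants might be hesitant to participate in the pilot study as participation might be perceived to harm their employment". It is plausible, though the article does not show it, that someone uneasy after answering this item in a workplace study would close the survey or be reluctant to approach a facilitator.

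**Working it through.** The protocol gives no figure to reproduce. The check is a reading of every section that touches the survey, the PHQ-ADS, completion and duty of care, plus one count.

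1. **Where the message appears.** Section 2.8.1 places it at the end of the survey. The condition about having reported ideation can be read as deciding who sees the message or who is urged to make contact. On either reading the position is the same.

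2. **Whether anything appears earlier.** No section describes a display straight after the item, on leaving the survey, or at any other point before the end. The full survey specification is not shown and may contain one.

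3. **Whether the PHQ-ADS comes last.** Section 2.5 lists eight standardised measures: WHO-5, PHQ-ADS, DSS, SPS-6, WPAI-GH, OLBI, ATSPPH and selected COPSOQ scales. The order of administration is not stated. The number of measures after the PHQ-ADS is 8 minus its position:

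| Position of the PHQ-ADS | Measures after it |
|---|---|
| Last (8th) | 8 − 8 = 0 |
| As listed (2nd) | 8 − 2 = 6 |
| First (1st) | 8 − 1 = 7 |

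 The listed order is only an illustration. The count also leaves out the other survey content in section 2.5 (for example sociodemographic, expectation and COVID-19 items), whose position is equally unknown.

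4. **Whether incomplete surveys are expected.** Section 2.7 plans to examine completeness, so incomplete data are foreseen. No rate of stopping mid-survey is given. The 60% attrition in section 2.2.3 is loss between baseline and follow-up, and cannot stand in for it.

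5. **Whether other support closes the gap.**
   - Contact details reach everyone, but they do not respond to the answer, and the leaflet offers them for questions.
   - Facilitated sessions put someone nearby, but the article does not say that facilitators see answers, so the participant would have to speak up.
   - Staff training is valuable, but no step connects it to an endorsed item.
   - Component B's advice is not available at baseline, because the questionnaires come before Hub access. It is available by follow-up.

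It follows that a participant who endorses the item and stops before the end would not see the message, unless an undescribed earlier display exists or nothing follows the PHQ-ADS. How many people this would affect cannot be calculated, because the rates of endorsing the item and of stopping afterwards are both absent.

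**The case against.** The strongest reply is that this rests on what a condensed article leaves out. Page order and display rules belong in the survey specification. Section 2.8.1 says that a message appears at the end, not that this is the only display or that other scales come after the PHQ-ADS. If the PHQ-ADS is last, there is nothing to correct. The range of 0 to 7 is simply every possible position, so it says nothing about the likely size. The plan to examine completeness could refer to skipped items or missed follow-ups, and someone who skips items but reaches the end still sees the message. It is also not settled which block the message closes, since section 2.5 speaks of three surveys and then describes the validated questionnaires separately. Meanwhile the safeguards add up: facilitated sessions, trained and supervised staff, contact details for all, and approval by each local ethics committee. Finally, a support message shown part-way through could affect later answers on stigma and help-seeking, and equal exposure before and after does not guarantee an equal effect.

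Much of this stands. The order and the stopping rate are unknown, the completeness plan is not specifically about stopping mid-survey, and the general safeguards are real. These points limit the priority. They do not remove the concern, because the end placement is something the article states, and none of the safeguards is triggered by the answer.

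**Conclusion.** The concern holds as a low-priority improvement, with medium confidence. The protocol places its only ideation-linked response where a participant who stops early would not meet it, and it describes no earlier display. The size is unknown: close to zero if nothing follows the PHQ-ADS, and otherwise dependent on how often people endorse the item and then stop. The conclusion assumes that the unseen survey specification has no earlier display and that some content follows the PHQ-ADS. It does not imply that participants are left without support.

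**What to change.** Keep the message at the end and also show the same message directly after the PHQ-ADS page, at baseline and follow-up. Preferably show it to all respondents, so that nobody is singled out in a facilitated session. If the PHQ-ADS is already the last page, it is enough to confirm that.

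The cost is one display rule in the existing Qualtrics survey, reusing the planned text. The downside is a possible slight influence on scales answered afterwards, such as the DSS or ATSPPH. Showing the message to everyone at both time points keeps the exposure the same before and after the intervention, although its effect need not be identical. The pilot is a natural moment for the change: evaluating the procedures and instruments is one of its objectives (section 1), and its findings on completeness will shape the surveys of the later cluster randomised trial.

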#### 2.8.2. Data Protection

Personal data, including participant name, will be collected to ensure a record is kept of all participants who give their informed consent to participation in the research study. However, personal data, including participant name, will be stored separately from the evaluation data they provide, will not be shared with third parties, or appear in any reports. Each participant will have a unique identification code which is the combination of responses to four personal questions which is generated to ensure data will be kept as confidential as possible [41]. It will be used (1) to link the user activity data with the evaluation data; (2) to link participant data from different time points; and (3) to ensure accuracy in the dataset by allowing the participant to access, correct, or withdraw any data that they submit to the study. Informed consent will also be recorded in compliance with GDPR. Data will be controlled and managed by MENTUPP consortium members based at KU Leuven.

## 3. Discussion

The MENTUPP intervention employs a multilevel approach that focusses on educating supervisors and employees about mental health at work, gives tools to supervisors that can be used to promote mental wellbeing at work and reduce risk factors in the psychosocial work environment, as well as individual oriented tools for coping with stress and supporting peers. Although multilevel approaches are often recommended, high quality studies testing multilevel approaches at the workplace are largely missing [36,70,95,96,97].

The MENTUPP intervention has been developed based on theoretical frameworks [22,23] by leading researchers in occupational mental health from across the EU and Australia. The intervention has involved the co-operation and consultation of key stakeholders in occupational health in the three occupational sectors to ensure that the tools are relevant and specific to their needs. The approach also involves SME management from the very beginning of the implementation of the MENTUPP intervention to encourage support for and uptake of organisational level approaches to improve mental health of employees in SMEs.

The results of this pilot study will provide a comprehensive overview of the implementation of such an intervention in a variety of contexts, languages, and cultures. The overall MENTUPP project will not only provide evidence-informed, tailored tools for employees and managers/owners of SMEs but will evaluate how useful the tools are and better understand the barriers for using these tools in real-life settings across the healthcare, construction, and ICT sectors. Furthermore, given that construction is a male-dominated industry and healthcare is generally female-dominated, this provides us with an added opportunity to understand the implementation of such an intervention with consideration of potential gender differences.

Adverse effects of participating in the pilot study include the effect of potential mental health related stigma and the risks associated with mental health issues [98]. Participants might be hesitant to participate in the pilot study as participation might be perceived to harm their employment. This risk will be mitigated by SME engagement with the online delivery of the MENTUPP Hub that can also be accessed in participants’ own time, and the strict confidentiality with which participant data will be treated with.

